## Abstract

**Background:**

Infections with respiratory viruses such as SARS-CoV-2 and influenza are significant international public health concerns. While patients with cancer remain the most vulnerable group, they show poor vaccine response in general. Immunological data in this population are limited and mainly focus on serological parameters. However, in these patients, cellular, and especially T-cell, responses often seem to be induced more reliably than humoral responses.

**Objective:**

To gain further insights into vaccine-induced immunity, the RESPONSE study will analyze the effect of early and late booster vaccination on humoral and cellular responses, with special focus on T cell–induced immune responses. In addition, we aim to investigate factors influencing humoral and cellular vaccine-induced immunity in patients with hematological and oncological malignancies, including state of disease, treatment, and demographic factors.

**Methods:**

Humoral immune responses will be assessed by measuring binding and neutralizing antibodies using standardized assays. Cellular immunity will be evaluated using functional assays such as flow cytometry and FluoroSpot, as well as in-depth analyses using additional exploratory assays as appropriate. Immune responses will be correlated with clinical parameters, including disease status, treatment, and demographic factors.

**Results:**

This study was initiated following ethics approval and is currently recruiting participants. Enrollment commenced on March 25, 2025, and is ongoing, whereas biosample collection and follow-up visits are nearing completion for most participants. Final data cleaning, dataset integration, and statistical analyses of adaptive immune responses are planned from the third quarter of 2026 onward.

**Conclusions:**

This study intends to lay a foundation for a structured translational research platform on vaccination to aim for best protection from infection by different respiratory pathogens. Long-term objectives are reaching best possible protection from vaccine-preventable disease with a first focus on influenza infection. In addition, we plan to investigate vaccine-induced immune responses to the recently approved respiratory syncytial virus vaccine using this platform and possibly extend this to further vaccines in the future. Urgent questions, such as the influence of different targeted therapies on vaccine immune response, will be part of these projects.

**Trial Registration:**

ClinicalTrials.gov NCT06612515; https://clinicaltrials.gov/study/NCT06612515

**International Registered Report Identifier (IRRID):**

DERR1-10.2196/88520

## Introduction

Respiratory virus infections are a significant cause of morbidity and mortality, particularly among immunocompromised patients. These infections are caused by a variety of viral pathogens, including influenza viruses, respiratory syncytial virus (RSV), parainfluenza viruses, adenoviruses, rhinoviruses, and coronaviruses, among others. In the general population, these infections typically result in self-limiting illnesses. However, in individuals with compromised immune systems, such as those undergoing chemotherapy, organ transplant recipients, patients with hematological malignancies, and those with HIV, the consequences can be severe and often life-threatening. For example, patients with hematological and oncological diseases are at elevated risk of severe morbidity and mortality from influenza infections. Compared to influenza-associated hospitalization rates in the general population (37.9 per 100,000 person-years for persons aged 50 to 64 years) [1], patients with cancer are hospitalized at a rate of 219 per 100,000 person-years for patients younger than 65 years [2].

The immune system plays a crucial role in defending against viral pathogens. Immunocompromised patients, due to either primary immune deficiencies or secondary immunosuppression (eg, from immunosuppressive therapies), show impaired immune responses that hinder the effective clearance of viral infections. This impairment can lead to prolonged viral shedding; increased risk of secondary bacterial infections; and more severe disease manifestations, including acute respiratory distress syndrome and multi-organ failure. The management of respiratory virus infections in immunocompromised patients requires a multidisciplinary approach. Prophylactic measures, including vaccination and the use of antiviral prophylaxis, are crucial in reducing the incidence of these infections [3-5].

Given the significant impact of respiratory virus infections on immunocompromised patients, ongoing research is crucial to improve preventive strategies. This research includes studies on viral pathophysiology, host immune responses, and the development of optimal vaccination schedules. The emergence of new viral pathogens such as SARS-CoV-2 underscores the importance of surveillance and preparedness in this vulnerable population [6,7].

Respiratory virus infections represent a major health concern for immunocompromised patients, necessitating comprehensive and specialized care [2,3,8]. Continued advancements in diagnostics, therapeutics, and preventive measures are vital to mitigate the impact of these infections and improve the quality of life and survival of immunocompromised individuals.

The management of respiratory virus infections in immunocompromised patients requires a multidisciplinary approach and prophylactic measures, including vaccination, to reduce the incidence and severity of these infections. However, the efficacy of vaccination is often suboptimal in immunocompromised individuals and not well assessed in clinical trials [9-13].

A poor humoral immunogenicity has been reported for most available vaccines in hematological patients [12,14-18]. In particular, the affection of the B-cell axis by disease, treatment, or both impacts humoral vaccine immune response [19].

The humoral vaccine-induced immune response facilitates early protection directly after vaccination, whereas long-term protection warrants antibody persistence as well as immune memory cells [20]. Data from immunocompetent persons suggest that the cell-mediated immune response may be a better correlate of protection against virus infections in vaccinated adult patients with poor immune responses [21,22] than humoral immunity due to its major role in recovery from infection and virus clearance [23].

Immunological data in patients with hematological malignancies are generally scarce and mainly focus on serological parameters. However, in these patients, cellular immunity and especially T-cell responses often seem to be induced more reliably than humoral responses, as observed in other immunocompromised populations [24] and for other vaccines [24,25].

To close this knowledge gap, we will perform an observational study to prospectively analyze the effect of early and late booster vaccination, with special focus on virus-specific T-cell responses. Samples will be collected from patients who have been vaccinated as part of clinical routine.

## Methods

### Study Design

The RESPONSE study is a prospective monocentric noninterventional study of vaccine efficacy in immunocompromised patients. The study was registered on ClinicalTrials.gov on September 19, 2024. All immunocompromised patients who are vaccinated or willing to be vaccinated against respiratory viruses in accordance with Robert Koch Institute guidelines will be eligible. Eligibility depends on agreement by signing an informed consent form (ICF). A total of 1000 patients are planned to be enrolled.

Participating departments will screen all immunocompromised patients for eligibility according to the following definition: for immunocompromised states, the classification by Wiedermann et al [26], the “stages of immunosuppression,” will be considered, and patients in stages 1 to 3 will be eligible for study inclusion.

Eligible patients will be approached and informed about the study by their physicians. Patients will receive both oral and written study information and will be given sufficient time to ask questions and consider participation prior to enrollment. If a patient agrees to participate and signs the ICF, basic data regarding vaccination history and underlying disease, among other variables, will be collected. Samples for the assessment of vaccine-induced immune response will be drawn at baseline and 1, 3, 6, and 12 months after vaccination (−7 days to +7 days). Study personnel will coordinate sample assessment schedules and inform the participating physicians of upcoming blood samplings. The samples will be taken on planned physician appointments together with regular laboratory assessment due to the underlying disease. Study-related blood sampling will be performed at the same time points and from the same vein puncture as for routine standard procedures. An amount of 30 to 40 mL will be obtained (1 serum and 2-3 ethylenediaminetetraacetic acid [EDTA] tubes, as shown in Figure 1). No additional interventions (eg, vein puncture) or treatments are foreseen as part of study participation.

**Figure 1 figure1:**
[figure not shown]
Sampling for analyses of vaccine-induced (VI) humoral and cellular immunity.

Blood samples will be stored pseudonymized and frozen at University Hospital Cologne (Translational Research for Infectious Diseases and Oncology [TRIO] building).

All therapies and diagnostics, including vaccinations, will be administered solely as part of clinical routine and as recommended by appropriate guidelines (eg, recommendations from the German Standing Committee on Vaccination [STIKO] by the Robert Koch Institute). The German Arzneimittelgesetz (Medicinal Products Act), which regulates interventional clinical trials involving medicinal products, hence does not apply to this noninterventional observational study, and participating physicians, therefore, do not require Good Clinical Practice (GCP) certification.

### Objectives

The study objectives are as follows: (1) to compare antibody titers between different subgroups of immunocompromised patients after vaccination against respiratory viruses, (2) to compare antibody response rates between different subgroups of immunocompromised patients after vaccination against respiratory viruses, (3) to analyze T-cell response after vaccination against respiratory viruses, (4) to investigate factors (such as age, sex, treatment, and underlying disease) influencing the humoral and cellular vaccine-induced immune response in patients vaccinated against respiratory viruses, and (5) to improve vaccination strategies to achieve better protection against vaccine-preventable diseases caused by different respiratory pathogens in high-risk populations.

### Data Collection

Every study participant will be given a pseudonym. Study personnel will capture the following data at study entry:

Patient characteristics—sex (male or female) and age (years)Details on vaccination against respiratory viruses—date and type of vaccinationFurther vaccination historyDetails of the underlying disease and its treatmentData on infections, clinical signs and symptoms, identified pathogens, hospitalization, and severity of infection, as well as outcome within the interval since the last study sample

Longitudinal clinical and immunological follow-up data will be collected during predefined study visits after vaccination. Humoral immune responses will be assessed via measurement of binding and neutralizing antibodies using standardized serological assays, whereas cellular immune responses will be evaluated using functional T-cell assays, including flow cytometry–based analyses and FluoroSpot assays. Immune response data will be correlated with clinical characteristics, including underlying disease, treatment regimen, vaccination timing, prior infections, and demographic variables, to identify factors associated with impaired or enhanced vaccine-induced immunity. Due to the exploratory and observational nature of the study, additional immunological analyses may be performed as scientifically appropriate to further characterize vaccine-induced immune responses in this high-risk population.

Data will be pseudonymized for documentation. Access to personal data by third parties is not possible. Nonpersonal data (age, gender, illness, and medication) are also recorded using a survey form linked to the pseudonymization number. Personal data (name and date of birth) are handwritten in a pseudonymization list alongside the pseudonymization number. The pseudonymization list, the survey form, and consent forms are securely stored in their original form at the TRIO building. All data and information are subject to the legal provisions of the Federal Data Protection Act, the European General Data Protection Regulation, and confidentiality obligations. Participants have the right to obtain information about personal data that are collected and processed as part of the study at any time. They also have the right to receive a free copy of their data. Furthermore, participants have the right to have incorrect personal data corrected, have their data deleted, or restrict the use of their data.

### Study Procedure

#### Site Specifications

In principle, all departments of University Hospital Cologne will be eligible to participate in this study. Informed consent will be obtained by treating physicians.

#### Sample Size

A sample size of 1000 participants is planned. Due to an observational cohort design, a formal sample size calculation is not applicable. This is due to the nature of the study, which focuses on observing and analyzing real-world data without predefined experimental conditions. As such, the study relies on available cohorts rather than a controlled intervention, and the sample size is determined by the population under observation rather than a statistical power analysis.

### Eligibility

#### Inclusion Criteria

Inclusion criteria are as follows: (1) signed ICF, (2) patients with immunosuppression either from treatment or underlying diseases, (3) adult patients who are vaccinated or willing to be vaccinated against respiratory viruses in accordance with current STIKO recommendations, and (4) application of the vaccine in accordance with the Summary of Product Characteristics and relevant guidelines.

#### Exclusion Criteria

The exclusion criterion is patients unwilling or ineligible for vaccination under current STIKO recommendations.

#### Participant Withdrawal Criteria

A participant may withdraw from the clinical trial at any time for any reason without consequences. Withdrawal from the study is permanent: once a participant withdraws, they shall not be allowed to enter the study again. Withdrawal from the study will have no influence on the availability of vaccination for that patient.

In case of premature withdrawal, the reason should be collected, but this is not obligatory.

In case of withdrawal, all blood samples will be destroyed according to data protection requirements. Data cannot be removed from already completed scientific analyses. A participant who withdraws from the trial will not be replaced.

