### Study Conduct

#### Titer Assessment

Blood samples for analysis of vaccine-induced immune response will be drawn at baseline and 1, 3, 6, and 12 months after vaccination (−7 days to +7 days).

Study personnel will coordinate titer assessment schedules and inform participating physicians of upcoming blood samplings. The samples will be taken on planned physician appointments together with regular laboratory assessment due to the underlying disease. Samples will be analyzed after the last follow-up of each patient.

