Missing data will be assessed regarding extent and pattern. If appropriate, missing values will be handled using multiple imputation or mixed-model approaches that allow for analysis under missing at random assumptions. Sensitivity analyses will be performed to evaluate the robustness of the findings. Due to the exploratory nature of several immunological analyses, multiplicity adjustment methods may be applied where appropriate to control for type I error.

All statistical analyses will be conducted using validated statistical software. Statistical significance will generally be defined as a 2-sided *P* value below .05.

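### Withdrawal before assay erases every immune measurement a participant has given, so the missing-at-random analysis can use only that person's clinical covariates

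*Protocol article*

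**What the plan says.** Four parts of the protocol article bear on this.

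- **Sampling and assay (Titer Assessment).** "Blood samples for analysis of vaccine-induced immune response will be drawn at baseline and 1, 3, 6, and 12 months after vaccination". The assays come later: "Samples will be analyzed after the last follow-up of each patient".
- **Withdrawal (Participant Withdrawal Criteria).** "In case of withdrawal, all blood samples will be destroyed according to data protection requirements". One exception concerns data: "Data cannot be removed from already completed scientific analyses". On reasons: "In case of premature withdrawal, the reason should be collected, but this is not obligatory". On numbers: "A participant who withdraws from the trial will not be replaced".
- **Data rights (Data Collection).** "participants have the right to have incorrect personal data corrected, have their data deleted, or restrict the use of their data". Deletion of data is something a participant may ask for; it is not described as an automatic result of withdrawing.
- **Analysis (Statistical Analysis and Data Management, Overview).** The primary outcomes are the size and time course of humoral and cellular responses, analysed longitudinally by mixed-effects models or generalized estimating equations. Where judged appropriate, missing values are to be handled by "multiple imputation or mixed-model approaches that allow for analysis under missing at random assumptions". Sensitivity analyses are also promised, without detail.

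**The concern.** Samples are banked and assayed late, and withdrawal destroys the bank. Someone who attends baseline and months 1, 3 and 6 and then withdraws has given four samples, yet contributes no immune result. In a repeated-measures design the earlier responses are usually the best predictors of the later ones, and they are what a mixed model or an imputation model would use for a person who leaves early. Here those values never come into existence.

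At stake are precision at every visit, the ability to correct for withdrawal that is related to response, and the ability to check whether withdrawers responded differently while they were still attending. The reason for withdrawal may be unrecorded too. Destruction cannot be undone, so no later analysis plan can repair the loss.

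**Working it through.** **Step 1: the rules side by side.** Assay follows the last follow-up, and destruction follows withdrawal. If withdrawal comes first, nothing has been assayed when the samples are destroyed. The exception for completed analyses does not help, because no analysis of that person's samples has been done. Blood-derived values are therefore missing at every visit. Clinical and demographic data are not covered by the destruction rule and remain unless the participant asks for deletion.

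**Step 2: what the models can use.** A mixed model of the immune outcome gains no outcome information from a person with no outcome value. Imputation can condition on covariates such as age, sex, malignancy subtype, disease activity and treatment, but not on earlier responses. Missing at random given covariates remains possible; missing at random given earlier responses cannot be used for these people.

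**Step 3: numbers affected.** The plan states no withdrawal rate, SD or power calculation, so there is no figure of its own to reproduce. For an assumed proportion w withdrawing before assay, 1000 × w participants lose all immune data. The standard error of a simple mean rises by the factor 1/√(1 − w), relative to everyone being measured. Among the 157 enrolled, w = 5%, 10%, 20% and 30% correspond to about 8, 16, 31 and 47 people.

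**Step 4: illustrative bias (400,000 simulated patients; every input is an assumption).**

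- Covariate X: binary, 40% prevalence.
- Month-1 response: Y1 = −0.8X + u, with u of SD 1.
- Month-12 response: Y12 = −0.3 − 0.8X + 0.7u + √(1 − 0.49)·e, with e of SD 1 (residual correlation 0.7).
- Withdrawal after month 1: logit P = a + s, where s is 0 (random), X (covariate-driven), −Y1 (poor responders leave) or +Y1 (good responders leave), and a is set to give w.
- Samples destroyed: regression of the response on X among those remaining, averaged over everyone. Results kept: the same with Y1 added.

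Bias is in units of the within-covariate SD, with samples destroyed and adjustment for X:

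| w | Lost of 1000 | SE factor | Poor responders leave: month 1 / month 12 | Good responders leave: month 1 / month 12 |
|---|---|---|---|---|
| 5% | 50 | 1.026 | +0.047 / +0.033 | −0.047 / −0.033 |
| 10% | 100 | 1.054 | +0.091 / +0.063 | −0.090 / −0.063 |
| 20% | 200 | 1.118 | +0.172 / +0.121 | −0.174 / −0.121 |
| 30% | 300 | 1.195 | +0.252 / +0.175 | −0.253 / −0.176 |

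When withdrawal is random or driven by X, the adjusted bias is within 0.001 SD at both visits. When month-1 results are kept, month-12 bias is within 0.001 SD in every scenario.

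**Step 5: consistency check.** With residual correlation 0.7, month-12 bias should be 0.7 times month-1 bias: 0.7 × 0.252 = 0.176, against 0.175 simulated; 0.7 × 0.047 = 0.033, as simulated.

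**The case against.** A reader might infer that responses will be overstated, that the missing-at-random plan cannot work, and that every patient who drops out loses all data. The documents support none of these.

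- **Direction.** Nothing gives a withdrawal rate or ties withdrawal to response. The same simulation gives upward, downward or no bias depending only on the assumed mechanism. Because assays are late, neither patient nor physician has a study result when withdrawal is decided, so direct dependence on titre is unlikely. Dependence would have to run through disease, treatment or other shared causes.
- **Adjustment.** Disease and treatment are recorded and are candidate covariates. If they explain withdrawal, adjusting for them removes the bias. The methods are planned only where appropriate, with sensitivity analyses, and they still serve missed visits and unusable samples among people who do not withdraw.
- **Scope.** The destruction rule is written for withdrawal. It is not stated for death, progression, transfer, loss to follow-up or missed visits. Assay is timed to each patient's last follow-up, not fixed at month 12, so samples from someone whose visits end early without withdrawal can already be assayed.
- **Data protection.** The rule is presented as a data-protection requirement, and the consent form, which may already offer graded options, is not shown.

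All of this limits the consequence. It does not remove the defect: under the rules as written, an active withdrawal before assay discards all of that person's primary-outcome data. Nor do the documents show that automatic destruction is the only compliant choice, since Data Collection describes deletion and restriction as rights to be exercised. Non-replacement adds little to the point, because the planned 1000 rests on no power calculation.

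**Conclusion.** The point holds in a limited form, as a moderate matter in an exploratory observational cohort. Participants who actively withdraw before assay leave no immune measurement at any visit, and analysis under missing at random must then rest on clinical covariates alone.

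The size and sign of any bias cannot be known from the documents. Under the stated assumptions it is about zero if withdrawal is random or explained by recorded covariates. At month 12 it is roughly 0.03 to 0.18 SD in either direction if withdrawal tracks early response at rates of 5% to 30%. The near-complete correction when results are kept depends on the simulated withdrawal acting through the month-1 response itself. If withdrawal ran through unrecorded causes, kept results should help but need not remove the bias entirely. Loss of precision needs no assumption about mechanism, only that some participants withdraw.

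**What to change.** In Participant Withdrawal Criteria and the consent form, offer two distinct choices:

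- **(a) Stop further visits.** Samples and data already collected are retained and assayed. The last visit attended becomes the last follow-up, so the assay-timing rule needs only a clarifying sentence.
- **(b) Revoke consent to use.** Samples are destroyed at the participant's request.

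State that death, loss to follow-up, transfer and missed visits do not trigger destruction. Record the date of stopping and, where the participant gives one, the reason.

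The cost is a protocol and consent amendment with ethics and data-protection review. No extra blood is needed and the right to destruction is kept. Participants already enrolled may stay on the present terms unless re-consented. With 157 of 1000 enrolled, the other 843 (1000 − 157) could join under the revised terms. Those who choose (b) will still be lost to the immune analysis, which has to be accepted and reported.
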